**Interventions:**

1. **Positive deviance (PD)-approach:**

The PD-program will be tested among caregivers of identified malnourished children with CP. The positive deviance inquiry (PDI) report detailing successful feeding and caregiving practices from positive deviant families of children with CP (from previous qualitative assessments) will be used to develop the positive deviance (PD) nutrition intervention program.

**Positive deviance nutrition rehabilitation intervention:**

The PD-program will run for 3-months with 2 weeks sessions (12 days) conducted in each month. Each day sessions will include a half hour education session and a one and half hour peer led cooking session. Education sessions will be introduced through situational discussions and illustrated by an educational medium such as an appropriate game or a message. Caretakers will learn how to rehabilitate their malnourished children under the supervision and the support of positive deviant caregivers. Children will be nutritionally assessed by trained nutrition assistants or clinician on the 1^st^, 6^th^, and 12^th^ day of the sessions and after three months.

Caregivers will learn how to prepare nutrient-rich meals for their children from locally available food identified during the PD-inquiry, and good feeding and hygiene practices. Caregivers will together prepare their own food menus based on the PD-inquiry good foods or what they can conveniently access but of equal nutritional value. The menus will include foods which are locally available and affordable and of balanced nutrient value. Food menus will be repeated at least twice within each monthly sessions. However, because the participating children in the PD program are malnourished, total calorie and protein intake in the menus will exceed the daily normal requirement. For sustainability, participating caregivers will contribute the foods and required ingredients during the sessions from those locally available. Caregivers will also learn how to be able to identify child malnutrition through clinical signs, and other common preventable illnesses in childhood. Names and anthropometric data from the sessions will be recorded so as to track changes in nutritional status[^6^](#_ENREF_6)^,^ [^7^](#_ENREF_7).

1. **Parent facilitator trainings.**

The Parent facilitator training (PFT) intervention is part of the wider CURIE community-based intervention study among children with CP at the IM-HDSS. The CURIE intervention study consists of an intervention and control group (1:1 ratio) selected from a previous cohort of surviving children with CP recruited in the CURIE follow-up study and other eligible children with CP selected from the Iganga Mayuge districts CBOs to make-up the desired sample size of 90 children with 45 children per arm. Ethical approval of the CURIE intervention study has been obtained at reference (SS 5173)

The parent facilitator training programme is based on the Malamulele Onward Carer-2-Carer program (https://www.malamuleleonward.org/online-resources/c2c-materials) in South Africa. The program is designed to be delivered by parents/caregivers of children with CP in seven workshops that aim to improve CP child’s participation and activities of daily living (e.g, eating, dressing, and play).

**Training parent facilitators**: Four primary caregivers of children with CP from Iganga are trained as parent facilitators by physical therapist. The training involves four weeks of training from a master trainer from Malamulele Onward, herself a parent of a child with CP. Each workshop is approximately two hours long and includes between 6-10 caregivers. Each workshop is led by two parent facilitators who work as a team. To ensure quality and consistency of the workshops, the Parent Facilitators follow a detailed manual adapted from the Malamulele Onward Carer-2-Carer Programme translated into *Lusoga*, the local language. For each workshop the Parent Facilitators have a workshop kit, which includes display materials. No therapist will be involved in the monthly parent-led workshops. Two weeks after the workshops, caregivers and their children will attend a therapist-led practical group session which will have the same theme as the parent-led workshop.

**Parent facilitator-led sessions:** Parent facilitator sessions are held at a convenient community center. At the start of parent facilitator led sessions, caregivers are given a pretest on their knowledge about CP and caring for a child with CP including basic nutrition knowledge. A similar post –test assessment will be done at the end of the training program. Parent facilitator trainings involve 7 sessions that expose caregivers to understanding CP and how to improve body functioning: session1: what is CP? session2: CP as a way of life, Session 3: Getting my child’s body ready to move, Session 4: Eating and drinking a healthy diet, Session 5: communication, Session 6: Play, and Session 7: Central visual impairment. The therapists conduct regular monitoring and evaluation site visits to rural communities where the parent facilitators are working for ongoing training and up-skilling[^19^](#_ENREF_19).

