**Study design:**

This will be a 2x2 factorial quasi-randomized controlled trial assessing the effects of the Positive deviance (PD) (Yes/No) and Parent facilitator training (PFT) (Yes/No) strategies within four experimental conditions: i) Both PD and PFT, ii) Only PD, iii) Only PFT, iv) Neither PD and nor PFT (controls).

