**Outcome measures**

**Primary outcome**: Nutritional status: The primary outcome measure will be a weight gain of >200grams in 12 days[^10^](#_ENREF_10) and ≥ 900g within 3 months.

**Secondary outcomes** will include change in anthropometric Z scores for any of weight, height and BMI, and MUAC classification measure, and Caregiving. The caregiver outcome measure will include a score of the questionnaire evaluating caregiver’s basic nutrition and feeding knowledge before and after the intervention.

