**Randomization and blinding:**

**Randomization of participants from the CURIE (Akwenda) intervention study**: Eligible children with CP in the intervention group of the CURIE intervention study will be randomly assigned to receive PFT conditions so as to create the “both PD and PFT”, and “only PFT” conditions, as these individuals will receive PFT by default of the CURIE study. Likewise, participants in the CURIE control group will be randomly assigned to receiving, the “only PD condition”, and the “control” (neither PD nor PFT) condition.

**Randomization of participants from other organisations:** Since not all the CURIE intervention study participants may be eligible to participate (malnourished), other eligible caregivers and their children with CP sampled from elsewhere in the study site will be allocated to either the PFT or control groups of the CURIE study arms based on home village vicinity to make up the required sample for each of the four experimental conditions. Research assistants will be provided with the allocation of all participants after the baseline survey.

In order to avoid contamination, participants in the CURIE-intervention study have been allocated to clusters depending on the village where they reside. Neighboring villages were clustered together to reduce contamination between groups resulting in two geographically defined groups matched for age, sex and motor function. Given the similarity in study sites of the CURIE- study and this study, participants in our study will be allocated based on the already determined CURIE-intervention or control group village clusters as earlier described to avoid contamination. Participants in the control condition will be on waiting list to receive the PFT intervention later owing to the design of the wider CURIE study arrangement.

**Blinding:** Evaluators will be blinded on group allocations so that parent facilitators and caregivers do not report their subjective outcome measures differently. A group of independent outcome assessors (evaluators), not involved in the intervention, will administer the outcome measures after the interventions. These examiners will be blinded to group allocation to avoid reporting bias.

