**Study Implementation plan:**

This study and preceding qualitative assessments will be implemented as follows: In the first month, a situation analysis (nutrition survey) will be conducted by trained data collectors or clinicians to identify well-nourished and malnourished children and adolescents with CP from selected organizations in the study area. In order to identify the unique practices of caregivers of well-nourished CP children identified from the nutrition survey, that set them apart from others within the same community, a qualitative survey will be conducted during the second month. From this qualitative survey, a Positive Deviance Inquiry (PDI) report that documents the identified successful practices and good foods will be generated. Based on the PDI report, a positive deviance (PD) program will be designed and evaluated against the Akwenda/CURIE caregiver training program (parent facilitator trainings -PFT) among malnourished CP children through a randomized clinical trial. The trial will be implemented for 3 months. Monthly Nutrition Education and Rehabilitation Sessions (NERS) for identified malnourished children and their caretakers under the PD program, and training sessions under the PFT program will be conducted concurrently. Monthly growth monitoring of all children in the study group will be done by an external team of assessors. In order to evaluate the main effect of the PD program and the PFT programs separately and in conjunction, data management, analysis and reporting will be done in the subsequent months.

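### The 12-day part of the primary outcome has a scheduled weighing only in the PD arms, so the PD effect and the interaction cannot be estimated on it

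*Protocol*

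**What the plan says.** Outcome measures: "The primary outcome measure will be a weight gain of >200grams in 12 days", joined by *and* to a gain of at least 900 g within 3 months.

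Positive deviance nutrition rehabilitation intervention: "The PD-program will run for 3-months with 2 weeks sessions (12 days) conducted in each month". Under the same heading, "Children will be nutritionally assessed by trained nutrition assistants or clinician on the" first, sixth and twelfth session days, and again after three months. It adds: "Names and anthropometric data from the sessions will be recorded so as to track changes in nutritional status".

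Three other places provide weights for all arms:
- Defining malnutrition: anthropometry at screening serves as baseline for everyone enrolled.
- Study Implementation plan: "Monthly growth monitoring of all children in the study group will be done by an external team of assessors".
- Randomization and blinding: independent evaluators, blinded to allocation and "not involved in the intervention, will administer the outcome measures after the interventions".

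Data management and analysis plans a two-way ANOVA for the main effects of PD and PFT and their interaction. Table 1 puts 31 children in each of the four cells.

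**The concern.** The 12 days in the primary outcome are the length of one PD session block, and the weighing that would measure them belongs to that block. Children in the PFT-only and control arms attend no PD sessions. The plan therefore makes a 12-day gain part of its primary outcome in a four-cell comparison but schedules the measurement in only two cells. A later analysis plan can define estimators, but it cannot supply weights that the visit schedule never collects.

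At stake is the PD contrast, which is the trial's main question, on one of the two components of its primary outcome. There is also a blinding issue. The blinded evaluators are provided for measures taken after the interventions, whereas the day-12 weights are taken during them, at a session that only PD families attend.

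**Working it through.** **The plan's own figure.** For two proportions, 0.64 v 0.29, two-sided α = 0.05, power 0.80, no continuity correction:

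n = [1.96·√(2·0.465·0.535) + 0.842·√(0.64·0.36 + 0.29·0.71)]² / 0.35² ≈ 30.7, so 31 per group and 62 for two groups.

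The precision formula gives 4·8·1·(1.96/2)² = 30.7, again 31. Four cells of 31 make 124. The figure reproduces, and this point does not change it. (Sample size estimation also mentions 32 per condition; the counts here follow Table 1 and the total of 124.)

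**What is scheduled in each cell.**

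| Cell | n | Baseline | Day 12 | Monthly | After the interventions |
|---|---|---|---|---|---|
| PD and PFT | 31 | yes | yes, at PD session | yes | yes |
| PD only | 31 | yes | yes, at PD session | yes | yes |
| PFT only | 31 | yes | none | yes | yes |
| Neither | 31 | yes | none | yes | yes |

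The PFT text does include a therapist-led group session two weeks after each workshop, but mentions no weighing there. The control arm has no sessions.

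Day-12 weight scheduled: 31 + 31 = 62. Not scheduled: 31 + 31 = 62, which is half of 124.

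**What the ANOVA can estimate on the 12-day component.** Write m(PD, PFT) for a cell mean, with 1 = yes and 0 = no.

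- PD main effect = ½[m(1,1) + m(1,0)] − ½[m(0,1) + m(0,0)]. The second bracket has no data.
- Interaction = [m(1,1) − m(1,0)] − [m(0,1) − m(0,0)]. The second bracket has no data.
- PFT effect within PD = m(1,1) − m(1,0). Estimable, 31 v 31.
- PFT main effect averaged over PD needs all four cells, so it is not available either.

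**If both thresholds must be met.** A child without PD who gains less than 900 g is a failure whatever happened by day 12. One who gains 900 g or more cannot be classified, because the 12-day condition is unknown. No child in the PD-No cells could then be scored a success.

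**The 3-month component.** Baseline and later all-arm weights exist in every cell, so all the ANOVA effects remain estimable.

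**The case against.** The strongest reply is that the measurement plan is fuller than the PD section suggests. All four arms have baseline, monthly and post-intervention weights, the 3-month criterion can be assessed in every arm, and PFT can still be compared within the PD arms at day 12. All of that stands, and it limits the point to the 12-day component. It does not close the gap, because none of those occasions yields a 12-day interval.

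A reader might infer more than the documents support:

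- *That programme staff take the day-12 weights in breach of the blinding rule.* The text says nutrition assistants or a clinician, and Data collection places a clinician on the data team. The blinding text covers measures after the interventions and does not clearly govern weighing during them. What can be said is that whoever weighs a child at a PD session would probably know that the child is in PD.
- *That substituting a monthly weight in the other arms would bias towards PD.* The direction is not established. Assume a steady gain that just reaches 900 g in 90 days, or 10 g a day: it gives 120 g in 12 days but 300 g in 30 days. Against a fixed 200 g threshold, the longer interval favours the arms without PD. Unblinded weighing might act the other way.
- *That PD children have three chances to pass.* The session block repeats monthly, but nothing says the threshold may be met in any block. The plan leaves the relevant block unstated, and any inflation figure would rest on a rule and a rate that it does not give.
- *That the caregiver-knowledge outcome has the same gap because* "caregivers are given a pretest on their knowledge about CP" *at the PFT sessions.* Outcome measures defines that score as before and after the intervention, without tying it to the PFT tests.

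**Conclusion.** The point holds for the 12-day component alone. As written, 62 of 124 children have no scheduled 12-day weight. The PD main effect and the PD by PFT interaction cannot be estimated on that component, and only PFT within PD (31 v 31) remains. This rests on reading the day 1, 6 and 12 assessments as part of the PD programme, as their placement and the reference to sessions indicate, and on the Table 1 cell sizes.

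How far it spreads depends on the word joining the two thresholds. If they are separate outcomes, the 3-month one is intact. If both must be met, the combined outcome cannot be determined for any child in the PD-No cells who gains 900 g or more. The probable lack of blinding at day 12 is a secondary weakness and no direction of bias is claimed. Because a primary-outcome component is unmeasured in two of four cells, this should be corrected before the trial relies on it.

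**What to change.** In Outcome measures, make weight gain at 3 months the sole primary outcome, measured in all four arms by the blinded independent assessors. State that this weight, and not the three-month assessment listed with the PD sessions, is the one analysed. Also state whether the external monthly team and the blinded evaluators are the same people, since the Protocol does not say. In the PD section, describe the day 1, 6 and 12 weights as process monitoring within PD, with no between-arm test.

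The cost is mainly wording, because the all-arm weights are already planned. The two proportions in the sample-size calculation are malnutrition prevalences, not 12-day gain rates, so this change alone does not require recalculating it. The real loss is the 12-day criterion, which comes from the PD study that Sample size estimation also cites for its assumed effect.

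If the sponsor wants to keep that criterion, the alternative is a baseline and day-12 weighing in all four arms on the same schedule by the blinded assessors, with the Protocol stating which 12-day window counts. That adds a visit for the 62 children without PD and a separate blinded weighing for the 62 with it.

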This study will be hinged on the cerebral palsy in Uganda risk factors, intervention and epidemiology (CURIE) research project which has implemented at the Iganga Mayuge health and demographic surveillance sites (IM-HDSS) in eastern Uganda since 2015. The CURIE project conducted the CP prevalence study in 2015 identifying 97 children with CP through a three stage screening process[^9^](#_ENREF_9). Ninety seven age and sex matched controls without CP were also recruited in 2015 for the CURIE follow-up study utilizing the CURIE prevalence study findings as baseline, and later conducting follow-up assessments in 2019. Using similar tools, gross and fine motor function, and nutrition and clinical examination assessments were made at the two points of assessment in 2015 and 2019 among the same study population of children with CP and their matched controls. An intervention study (Akwenda) was there after conducted by the CURIE study team between 2021 and 2022 in which effectiveness of a comprehensive intervention among surviving children with CP was tested. The Akwenda intervention included a Carer-to-Carer approach (parent facilitator trainings) on child functional outcomes, and caregiver quality of life, and a communication and advocacy intervention to improve community perceptions towards CP. The current study will utilize the CURIE intervention study arms to answer its intended objectives while using the same study population.

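### The Protocol contradicts itself on when parent facilitator training (PFT) is given relative to baseline and the 3-month reading, so the 3-month PFT effect and interaction cannot be read as those of the full programme

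*Protocol*

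**What the plan says.** Four parts of the Protocol bear on the timing of PFT.

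- **Parent facilitator trainings (Interventions).** "Parent facilitator trainings involve 7 sessions that expose caregivers to understanding CP and how to improve body functioning". The diet topic is fourth: "Session 4: Eating and drinking a healthy diet". The workshops are described as monthly: "No therapist will be involved in the monthly parent-led workshops". A practical on the same theme follows each one: "Two weeks after the workshops, caregivers and their children will attend a therapist-led practical group session".
- **Study Implementation plan.** "The trial will be implemented for 3 months", and within it "training sessions under the PFT program will be conducted concurrently" with the PD sessions.
- **Introduction.** The Akwenda intervention study, which included PFT, was "conducted by the CURIE study team between 2021 and 2022".
- **Randomization and blinding.** Written in the future tense: families in the CURIE intervention arm are going to receive PFT because that study provides it, and control families wait to receive it later. Families recruited from elsewhere join the PFT or control side according to their village.

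Under Outcome measures, "The primary outcome measure will be a weight gain of >200grams in 12 days", together with a gain of at least 900 g within 3 months. Data management and analysis tests the main effects of PD and PFT and their interaction in one two-way ANOVA.

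**The concern.** PFT is one of the two factors of the 2x2 design. Its main effect and its interaction with PD have a clear meaning only if the reader knows how much PFT the PFT-Yes families have had by the time weight is read, and how much of it came before the baseline weight. The Protocol gives incompatible answers: seven monthly workshops, a 3-month concurrent programme, a programme already carried out, and a programme still to come.

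A small or null PFT contrast could then mean that PFT does not affect weight, that the feeding content had not yet been taught, or that part of the effect was already in the baseline weight. The PD-plus-PFT cell could also combine families trained well before baseline with families starting afresh.

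**Working it through.** **Inputs.** Seven workshops, monthly, diet as number 4, practical two weeks later (Parent facilitator trainings); primary readings at 12 days and 3 months (Outcome measures); 3-month trial (Study Implementation plan); 45 children per CURIE arm (Parent facilitator trainings); 31 per cell (Table 1); 64% malnourished in 2015 (Sample size estimation). The Protocol gives no calendar date for this trial and does not tie workshop 1 to its baseline, so the start is left free. There is no planned figure for the schedule to reproduce.

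**Step 1: timeline.** Let workshop 1 be held at month s relative to baseline. Workshop k is then at month s + (k − 1), and its practical half a month later.

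| Start s | Workshop 4 (diet) | Its practical | Workshop 7 | Held before month 3 | Held by month 3, reading day included |
|---|---|---|---|---|---|
| 0 | 3.0 | 3.5 | 6.0 | 3 | 4 |
| 0.5 | 3.5 | 4.0 | 6.5 | 3 | 3 |
| 1 | 4.0 | 4.5 | 7.0 | 2 | 3 |

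For any start at or after baseline, the diet workshop falls on or after the last weight reading and its practical falls after it. By day 12 at most workshop 1 has been held.

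**Step 2: could seven fit into 3 months?** Seven workshops in 90 days need a spacing of 90/6 = 15 days, with workshop 4 at day 45. That is not monthly.

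**Step 3: PFT already under way at baseline.** The diet workshop falls after baseline and before month 3 if 0 < s + 3 < 3, that is −3 < s < 0. Completion by month 3 needs s + 6 ≤ 3, that is s ≤ −3. The two conditions exclude each other. On a monthly schedule, either the diet workshop is inside the window and the programme is unfinished at month 3, or the programme is finished and the diet workshop was held on or before the baseline day.

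**Step 4: PFT completed before baseline.** The baseline weight then already contains any earlier effect, and the change to month 3 may capture only a residual one. This applies only to families who were in the CURIE intervention arm.

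**Step 5: how many families are new.** PFT-Yes needs 31 + 31 = 62.

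- If all 45 children in the CURIE arm qualify: 62 − 45 = 17 new families, 17/62 = 27%.
- Assuming the 64% rate applies: 0.64 × 45 ≈ 29 qualify, 62 − 29 = 33 new families, 33/62 = 53%.

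The 64% is an assumption here. Exclusion of severe cases or refusals would raise the share of new families.

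**Step 6: knowledge score.** The PFT post-test comes at the end of the training. With monthly workshops from baseline this is month 6 or later, outside the 3-month trial, yet caregiver knowledge before and after the intervention is a secondary outcome.

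**The case against.** A reader might infer that the 3-month reading misses the nutrition content of PFT whichever section is right, and that the expected PFT effect is close to zero. The documents do not support this.

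- The two cases, PFT starting at baseline and PFT finished before it, are not exhaustive. The trial is undated, and PFT could be in progress at baseline with the diet workshop inside the window (Step 3).
- Caregivers trained earlier keep what they learned, so weight gain after baseline can still reflect it. Earlier training may dilute the contrast; it need not remove it.
- Nothing in the Protocol says that PFT acts on weight mainly through the fourth workshop. The workshops as a whole aim at daily activities, eating among them.
- The evidence that PFT was already over is a past-tense sentence in background text, and the Protocol mixes tenses elsewhere: the limitations section reports in the past tense an adjustment that had yet to be made.

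All four points stand, and they limit the finding. It would also be too strong to call the contrast uninterpretable, since it can be read as the effect of PFT delivered by month 3. None of this removes the contradiction. The favourable in-progress case is not stated anywhere, and even there the full monthly programme does not fit between baseline and month 3. Nor is this detail that belongs in an SAP: when an intervention is given relative to baseline and endpoint is for the Protocol to fix.

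**Conclusion.** The point holds as a contradiction about exposure. The Introduction, Parent facilitator trainings, Randomization and blinding, and Study Implementation plan do not agree on when PFT is delivered relative to baseline and the 3-month reading. Seven monthly workshops span at least 6 months against a 3-month trial. If they start at baseline, two or three precede the final reading, with one more on the reading day at most, and the diet workshop is on or after that day. If CURIE families were trained earlier, at least 27% of PFT-Yes (about 53% if the 64% rate applies) have a different exposure timing from the rest. The 3-month PFT main effect and the PD by PFT interaction should therefore not be reported as effects of the seven-session programme.

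This rests on reading monthly as one workshop per month and on the cell sizes in Table 1. The documents give no expected PFT effect on weight, so the size of any dilution cannot be stated. Which schedule is right is not judged here.

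**What to change.** - Reconcile the four sections so that the timing of PFT relative to baseline and to the 3-month reading is stated once. The schedule is for the sponsor to settle.
- Record for each family the PFT workshops attended before baseline and by month 3.
- State the 3-month PFT contrast and the interaction as effects of the workshops delivered by then, not of the seven-session programme.
- Include recruitment source (CURIE or external) as a factor in the model. It exists on both sides of the PFT factor, so it can be adjusted for.
- Report PFT received before baseline descriptively, or as a subgroup within PFT-Yes. It should not be a main-effect covariate: waiting-list controls have none, so it is nested in PFT-Yes, and adjusting for it would turn the PFT main effect into that of new recruits only.

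The cost is an attendance field, one model term and a narrower PFT claim. A PFT reading after the last workshop would be a larger change. With monthly workshops from baseline it would come at month 6 or later, would keep waiting-list controls untrained and under follow-up for longer, and would affect the interaction test, so it is not needed to resolve this point.
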